## Methods

This protocol includes the standard protocol items recommended for interventional trials according to the Standard Protocol Items: Recommendations for Interventional Trials (SPIRIT) guidelines (online supplementary file 1).^27^

10.1136/bmjopen-2019-035326.supp1Supplementary data

### Design

This randomised controlled trial is currently being performed at the departments of Gastroenterology and Hepatology in 21 hospitals in the Netherlands, including both academic and non-academic centres. The aim of the adalimumab interval lengthening strategy is to minimise the amount of adalimumab use while maintaining remission in CD. Therefore, longer adalimumab intervals will be compared with adalimumab EOW in a non-inferiority design (to show the same effect is maintained with a dose reduction strategy), instead of a superiority design, which is used to demonstrate that an intervention leads to superior outcomes than the standard of care. The rationale behind a non-inferiority design is that benefits may be present in other areas (ie, fewer side effects, lower costs) so that the intervention would be preferred if its efficacy is not worse.

The date of the first enrolment was 3 May 2017. The study is approved by the Medical Ethical Committee (METC) Arnhem-Nijmegen (registration number NL58948.091.16). Important protocol modifications are assessed and approved by the METC, and reported to participating investigators. The most recent study protocol version 3.3 (July 2018) is presented in this manuscript. The Lengthening Adalimumab Dosing Interval (LADI) study has been registered at clinicaltrials.gov and the Dutch trial registry. A data safety monitoring board is installed in order to independently assess the efficacy and safety of the study intervention and to monitor the overall conduct of the trial. Prior to enrolment, all patients have to sign informed consent (online supplementary file 2).

10.1136/bmjopen-2019-035326.supp2Supplementary data

### Patient and public involvement

The study was designed in collaboration with the Dutch Crohn’s and colitis patient organisation (CCUVN) in order to optimise patient participation. We based our study design on the results of a *biological focus group* by members of the CCUVN. This focus group showed that patients do accept a reduction of the dose of their biological agent. Additionally, based on previous interactions with the CCUVN, we have included patient focused outcomes in our study, such as the quality of life and PRO-2.

### Inclusion and exclusion criteria

All adult CD patients with colonic and/or distal ileal and/or proximal CD, who are treated with adalimumab 40 mg every 2 weeks at a stable dose, at least 9 months in steroid-free clinical remission and not scheduled for CD-related surgery, are eligible for participation.^28^ Remission is defined as an HBI <5, FC <150 µg/g and CRP <10 mg/L. The current guidelines from the European Crohn’s and Colitis Organisation (ECCO) suggest to use CRP <10 mg/L for the definition of disease remission.^5^ Endoscopic assessment prior to enrolment is not mandatory, however if an ileocolonoscopy was performed before the start of the study and demonstrated complete mucosal healing (Simple Endoscopic Score-CD <3 or no ulcerations), an FC <250 µg/g is accepted as inclusion criterium. Permitted concomitant CD therapies are: aminosalicylates, azathioprine, 6-mercatopurine, methotrexate and thioguanine at a stable dose for 12 weeks. Patients with arthralgia will be included, however inflammatory arthritis is an exclusion criterium, as this can provide elevated inflammatory markers. Furthermore, patients with active draining fistulas are excluded. Other exclusion criteria are pregnancy or lactation and other significant medical conditions that might interfere with this study (such as a current/recent malignancy, immunodeficiency syndromes and psychiatric illness), or when it is to be expected that the outcome cannot be measured (short life expectancy, planned major surgery, language issues).

### Study groups

#### Control group

The control group continues maintenance treatment with adalimumab sc 40 mg EOW. Treatment decisions are made at the discretion of the treating physician. Of note, dose reduction beyond 40 mg per 2 weeks is currently not recommended according to national guidelines.^29^ Patients follow a standardised protocol based on the tight control/treat-to-target principle in order to maintain low disease activity.^16^

#### Intervention group

Adalimumab interval will be lengthened through a stepwise disease activity guided manner.

Step 1: On inclusion, the interval will be prolonged to ETW.

Step 2: After week 24, patients in remission will lengthen their dosing interval to EFW.

Step 3: If adalimumab interval lengthening leads to a confirmed flare, patients will return to the preceding effective interval (figure 1). If a flare is not objectively confirmed, patients are advised to continue adalimumab in their study-interval. However, interval reduction is accepted if patients really want this as this situation reflects daily clinical practice.

**Figure 1 F1:**
[figure not shown]
Protocolised treatment recommendation in case of disease flare. T0: start of possible disease flare, which can occur at any time during follow-up, T2: 2 weeks after T0, T6−8: 6–8 weeks after T0. Lab tests include haemoglobin, leucocytes, thrombocytes, albumin, C-reactive protein, calprotectin.

In contrast to the DRESS study, the discontinuation of therapy after successful de-escalation to 40 mg EFW is not implemented in the study protocol.^21^ Total follow-up time will be 48 weeks. Follow-up visits and outcome measurements are similar to the control group.

### Cointervention

The use of previously mentioned concomitant medication is allowed and must be documented on the case-report form (CRF) (stating type, dosage and duration). If possible, existing concomitant medication should not be changed during the study.

If patients experience worsening of symptoms in between visits, they must contact the outpatient clinic. For further treatment of the flare, patients in the control arm are referred to their treating physician. In the intervention arm, patients will return to the preceding effective adalimumab dosing interval (figure 1). The decision to start concomitant therapy remains at the discretion of the treating physician.

### Secondary outcome measurements

#### Quality of life

For assessment of quality of life, we will use the SIBDQ, which is a validated and disease-specific questionnaire.^30^

#### Patient reported disease activity

We will use the only validated IBD patient-reported outcome measure, ‘PRO-2’, consisting of reported diarrhoea and abdominal pain.^31^

#### Factors associated with successful dose reduction

Factors which are possibly related to successful dose reduction include: baseline patient and treatment characteristics, adalimumab drug levels (µg/mL) and antibodies (AU/mL), clinical (physician global assessment, HBI) and laboratory results (FC (µg/g), CRP (mg/L), haemoglobin (g/L), leucocytes (10^9^/L), platelets (10^9^/L), albumin (g/L)).

#### Safety

AEs and SAEs are registered during follow-up. All SAEs are reported to the METC Arnhem-Nijmegen.

#### Cost-effectiveness

The impact of dose reduction on the quality of life of patients will be assessed by the EuroQuol-5D (EQ-5D) at 24 and 48 weeks following randomisation, compared with baseline. The EQ-5D utility will be used to derive a quality-adjusted life year (QALY) estimate for each patient according to the trapezium rule.^32 33^

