### Assessments

Enrolled patients will visit the outpatient clinic every 24 weeks. If preferred by the patient or treating physician, the evaluations at week 12 and 36 can take place as outpatient clinic visit as well. Every 12 weeks, laboratory tests (eg, FC, CRP, haemoglobin and albumin) will be performed. At week 0, 24 and 48 serum samples are stored for measurement of adalimumab drug levels and antibodies to adalimumab. Additionally, patients in both arms will be interviewed via telephone every 6 weeks in between clinical visits to assess for adverse events, symptoms and potential disease activity. If such an interview suggests a disease flare, patients must visit the outpatient clinic in order to undergo complete disease activity assessment and laboratory and FC tests. If patients have a flare at week 48, disease activity will be monitored until disease remission, in order to define the flare as persistent- or transient flare. In addition, study questionnaires are automatically sent via Castor every 12 weeks. During follow-up, patients register the adalimumab injection dates in a study-diary and bring this to the outpatient clinic every visit to evaluate adherence to adalimumab. An overview of all visits and assessments is depicted in table 1 and figures 1 and 2.

**Table 1 T1:** SPIRIT schedule of enrolment, interventions and assessments

	Study period											
	Enrolment	Allocation	Follow-up									Extra
Timepoint	−t_1_	0	w_0_	w_6_	w_12_	w_18_	w_24_	w_30_	w_36_	w_42_	w_48_	w_e_
Enrolment												
Eligibility screen	X											
Informed consent	X											
Allocation		X										
Interventions												
*Intervention: lengthening adalimumab dosing interval*											
*Control: adalimumab every other week*												
Assessments												
*Medical history*	X	X										
*Laboratory tests**			X		X		X		X		X	X
*Faecal calprotectin*			X		X		X		X		X	X
*Storage of serum samples*			X				X				X	X
*Concomitant medication*			X	X	X	X	X	X	X	X	X	X
*(Serious) adverse events*			X	X	X	X	X	X	X	X	X	X
*Physician global assessment*			X	X	X	X	X	X	X	X	X	X
*HBI*			X		X		X		X		X	X
PRO-2, *IBD-Q and EQ5D*			X		X		X		X		X
*iMTA MCQ, PCQ*			X		X		X		X		X

*Haemoglobin, leucocytes, thrombocytes, albumin, C-reactive protein.

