#### Cost-effectiveness analysis

The cost analysis consists of two main parts. First, at patient level, volumes of care related to the CD care and anti-TNF therapy will be measured by means of the iMTA MCQ. This questionnaire measures all relevant healthcare related costs like outpatient visits at any medical specialist, hospitalisations and imaging procedures. Loss of productivity due to illness or recovery in patients below the age of 65 years will be estimated based on patient reported absences from paid (or unpaid) labour measured with the PCQ. The second part of the cost analysis consists of determining the cost prices for each volume of consumption. The standard cost prices from the ‘Dutch Guidelines for Cost Analyses’ and www.medicijnkosten.nl will be used. For units of care where no standard prices are available real costs prices will be determined on the basis of full cost pricing. Productivity losses will be valued by means of the friction cost method. In the end volumes of care will be multiplied with the cost prices for each volume of care to calculate costs. Because we anticipate non-inferiority of the dose reduction strategy, we will primarily analyse cost-savings: direct medical cost as well as total costs (medical and non-medical costs) will be compared between intervention and control group. A possible small but acceptable loss of effect can be incorporated in the analyses by determining a decremental cost-effectiveness ratio (DCER) by dividing the difference in costs by the difference in QALYs between the groups. The DCER expresses with how much money a loss of one QALY is compensated. If this amount is high the decision makers may be willing to accept a loss of effect. Uncertainty in the DCER will be non-parametrically determined using bootstrap techniques (1000 replications). Results from this analysis will be presented in a scatter plot and willingness to pay (or accept) curve. Furthermore, the Net Monetary Benefit per patient will be calculated for different levels of willingness to accept (WTA) in euro’s per QALY, using the formula: WTA×effect (difference in QALY)−costs. This results in the net amount of money saved, when the possible loss of QALY is corrected for, using different WTA levels per QALY.

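### The DCER and Net Monetary Benefit rest on a QALY difference for which no baseline-utility adjustment is named; adding one is free and makes the estimate more precise

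*Protocol article*

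**What the plan says.** Under Secondary outcome measurements, Cost-effectiveness, the Protocol article says that the effect of dose reduction on quality of life is "assessed by the EuroQuol-5D (EQ-5D) at 24 and 48 weeks following randomisation, compared with baseline". It goes on: "The EQ-5D utility will be used to derive a quality-adjusted life year (QALY) estimate for each patient according to the trapezium rule".

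Under Planned data analysis, Cost-effectiveness analysis, the DCER is obtained by "dividing the difference in costs by the difference in QALYs between the groups". The Net Monetary Benefit multiplies the same QALY difference by a willingness-to-accept value and subtracts costs. Uncertainty comes from a non-parametric bootstrap with 1000 replications. No covariate is named for either quantity.

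Elsewhere the article does name adjustment. The primary analysis is adjusted for comedication by Cochran-Mantel-Haenszel. Repeated-measures analyses of several continuous outcomes may be corrected for the baseline value, but the QALY is not listed among them. Randomisation is stratified on comedication only.

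On timing, the Assessments section says that "study questionnaires are automatically sent via Castor every 12 weeks", and Table 1 shows EQ-5D at weeks 0, 12, 24, 36 and 48. The Cost-effectiveness section names only baseline, week 24 and week 48.

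**The concern.** A trapezium area measures the level of utility over follow-up, not change from baseline. The week-0 value is its first ordinate, and patients who start higher tend to stay higher. A chance gap in week-0 utility between the arms therefore enters the QALY difference twice: directly through the first ordinate, and indirectly through the later values correlated with it.

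The article expects at most a small loss of effect. The QALY difference is then a small denominator in the DCER, and its sign decides whether the result reads as a loss compensated by savings or as a gain. Noise that could be removed at no cost matters more in that setting than it would for a large effect.

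**Working it through.** **Inputs from the article.** Planned total 174, allocated 2:1, which gives 174 × 2/3 = 116 and 58. Follow-up is 48 weeks, or 48/52 = 0.923 year. The stated sample size reproduces: (1.64 + 0.84)² × 0.15 × 0.85 × 1.5 / 0.15² = 52.3 control and 104.6 intervention, rounded up to 53 and 105; 158 × 1.1 = 173.8, or 174. The article gives no figure for EQ-5D, QALY or DCER.

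**Assumptions.** EQ-5D SD 0.12 to 0.20; equal correlation ρ between any two visits of 0.5 to 0.7, with ρ = 0 as the lower bound; all 174 patients contribute.

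**Trapezium weights, as fractions of the 0.923-year area.**
- Weeks 0/24/48: 0.25, 0.5, 0.25. The week-0 value carries 25%.
- Every 12 weeks: 0.125, 0.25, 0.25, 0.25, 0.125. The week-0 value carries 12.5%.

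**Formulas.** Let w be the weights, w₀ the week-0 weight and R the correlation matrix.
- SE of the chance week-0 gap: SD × √(1/116 + 1/58), which is 0.019 at SD 0.12 and 0.032 at SD 0.20.
- Carry-over c = w₀ + ρ(1 − w₀). Slope of the QALY difference on the week-0 gap = 0.923 × c.
- Share of variance removed by adjustment: c² / (wᵀRw).
- SE of the unadjusted QALY difference: 0.923 × √(wᵀRw) × SE of the gap. Adjusted SE: that value × √(1 − share removed).
- Chance of a wrong sign when the true loss is 0.01 QALY: Φ(−0.01/SE).

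**Worked example (0/24/48, ρ = 0.5, SD 0.20).** c = 0.25 + 0.5 × 0.75 = 0.625, slope 0.577, wᵀRw = 0.6875. Share removed = 0.625²/0.6875 = 57%. SE falls from 0.0246 to 0.0162. A one-SE week-0 gap of 0.032 shifts the unadjusted QALY difference by 0.577 × 0.0322 = 0.0186.

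| Schedule | ρ | Slope | Variance removed | SE, SD 0.12 (unadj. → adj.) | SE, SD 0.20 (unadj. → adj.) | Wrong sign, SD 0.12 | Wrong sign, SD 0.20 |
|---|---|---|---|---|---|---|---|
| 0/24/48 | 0.5 | 0.577 | 57% | 0.0148 → 0.0097 | 0.0246 → 0.0162 | 25% → 15% | 34% → 27% |
| 0/24/48 | 0.7 | 0.715 | 74% | 0.0161 → 0.0082 | 0.0268 → 0.0137 | 27% → 11% | 35% → 23% |
| 12-weekly | 0.5 | 0.519 | 52% | 0.0139 → 0.0096 | 0.0232 → 0.0161 | 24% → 15% | 33% → 27% |
| 12-weekly | 0.7 | 0.681 | 71% | 0.0156 → 0.0084 | 0.0260 → 0.0140 | 26% → 12% | 35% → 24% |

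With SEs rounded to three decimals (0.014 to 0.027 unadjusted, 0.008 to 0.016 adjusted), the wrong-sign ranges are about 24%–36% and 11%–27%. Within a row, the reduction is about 7 to 16 percentage points. At ρ = 0 the variance removed is only 17% (0/24/48) or 7% (12-weekly).

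**Simulation with no true effect** (10,000 trials; 0/24/48, SD 0.20, ρ = 0.5). The unadjusted difference averaged 0.000 over all trials. In the 18% of trials with a week-0 gap above +0.03 (mean gap 0.048), it averaged +0.028, against +0.001 for the adjusted estimate.

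**The case against.** The article never says that the comparison is unadjusted. A regression-adjusted difference is still a difference between the groups, and a condensed article may leave the covariates to a fuller protocol or analysis plan. A reader might infer that the trial has decided to ignore baseline utility; the text does not support that. What stands is narrower: the formulas that are given contain no baseline term, although the article does name adjustment for other outcomes.

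The trapezium rule itself is not at fault, and the fix keeps it. Nor does the phrase about comparison with baseline amount to a promise that the next sentence breaks. It concerns how quality of life is assessed and does not say how the QALY difference is estimated.

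A reader might also infer that the planned QALY comparison is biased. It is not: over repeated randomisation the unadjusted difference is unbiased, and the bootstrap honestly reports its extra variability. The loss is in precision and in dependence on the realised imbalance. Two patients stable at 0.80 and 0.90 would differ by 0.09 QALY with no treatment effect, but that compares individuals and says nothing about the gap between randomised arms.

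Finally, imbalance taken alone would push a true 0.01 loss past zero in about 16% to 33% of trials (SD of the carried imbalance 0.010 to 0.023). That is not the gain from adjustment, because other sampling noise remains. The before-and-after comparison in the table is the relevant one.

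**Conclusion.** The point holds as a free improvement to a secondary analysis. As written, the formulas lead to a QALY difference that is unbiased over randomisation, less precise than the planned data allow, and biased conditional on any week-0 gap. The gain is substantial if utilities correlate at 0.5 to 0.7 across visits and modest if they hardly correlate. The SD, the correlation and the 0.01 loss are all assumptions.

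The primary endpoint and the sample size are untouched. The article also ranks cost savings ahead of the DCER, so the leading economic comparison does not depend on this point. Separately, the EQ-5D time points for the QALY differ between the Cost-effectiveness section and Table 1. The choice halves or doubles the weight of the week-0 value and needs to be settled.

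**What to change.** In the Cost-effectiveness analysis section, state that the QALY difference is estimated by linear regression of each patient's trapezium QALY on arm, week-0 EQ-5D utility and comedication stratum. Refit the model in each of the 1000 bootstrap replicates, keeping each patient's costs and QALY together. Use the adjusted difference in the DCER, the scatter plot, the willingness curve and the Net Monetary Benefit. Report the unadjusted difference as a sensitivity analysis.

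State once which EQ-5D time points enter the QALY, and make the Cost-effectiveness section and Table 1 agree.

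The cost is a sentence or two of text and one regression per replicate. Week-0 EQ-5D is already scheduled in Table 1, so no new data are needed.

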### Assessments

Enrolled patients will visit the outpatient clinic every 24 weeks. If preferred by the patient or treating physician, the evaluations at week 12 and 36 can take place as outpatient clinic visit as well. Every 12 weeks, laboratory tests (eg, FC, CRP, haemoglobin and albumin) will be performed. At week 0, 24 and 48 serum samples are stored for measurement of adalimumab drug levels and antibodies to adalimumab. Additionally, patients in both arms will be interviewed via telephone every 6 weeks in between clinical visits to assess for adverse events, symptoms and potential disease activity. If such an interview suggests a disease flare, patients must visit the outpatient clinic in order to undergo complete disease activity assessment and laboratory and FC tests. If patients have a flare at week 48, disease activity will be monitored until disease remission, in order to define the flare as persistent- or transient flare. In addition, study questionnaires are automatically sent via Castor every 12 weeks. During follow-up, patients register the adalimumab injection dates in a study-diary and bring this to the outpatient clinic every visit to evaluate adherence to adalimumab. An overview of all visits and assessments is depicted in table 1 and figures 1 and 2.

**Table 1 T1:** SPIRIT schedule of enrolment, interventions and assessments

	Study period											
	Enrolment	Allocation	Follow-up									Extra
Timepoint	−t_1_	0	w_0_	w_6_	w_12_	w_18_	w_24_	w_30_	w_36_	w_42_	w_48_	w_e_
Enrolment												
Eligibility screen	X											
Informed consent	X											
Allocation		X										
Interventions												
*Intervention: lengthening adalimumab dosing interval*											
*Control: adalimumab every other week*												
Assessments												
*Medical history*	X	X										
*Laboratory tests**			X		X		X		X		X	X
*Faecal calprotectin*			X		X		X		X		X	X
*Storage of serum samples*			X				X				X	X
*Concomitant medication*			X	X	X	X	X	X	X	X	X	X
*(Serious) adverse events*			X	X	X	X	X	X	X	X	X	X
*Physician global assessment*			X	X	X	X	X	X	X	X	X	X
*HBI*			X		X		X		X		X	X
PRO-2, *IBD-Q and EQ5D*			X		X		X		X		X
*iMTA MCQ, PCQ*			X		X		X		X		X

*Haemoglobin, leucocytes, thrombocytes, albumin, C-reactive protein.

EQ-5D, EuroQuol-5D; HBI, Harvey Bradshaw Index; IBD-Q, Inflammatory Bowel Disease Questionnaire; iMTA MCQ, institute for Medical Technology Assessment Medical Consumption Questionnaire; PCQ, Productivity Cost Questionnaire; PRO-2, patient reported outcome-2; SPIRIT, Standard Protocol Items: Recommendations for Interventional Trials.

**Figure 2 F2:**
[figure not shown]
Schematic presentation of the trial design. ADA, adalimumab; W0, week 0; W6, week 6 and so on. Lab tests include haemoglobin, leucocytes, thrombocytes, albumin, C-reactive protein, calprotectin.

### Randomisation, allocation concealment, stratification

Patients are randomised by the research physician using a computer-generated randomisation system (Castor). Castor uses a validated variable block randomisation model with block sizes of 6, 9 and 12. Patients will be randomised in a 2:1 ratio for the intervention or the control group, respectively. We chose 2:1 randomisation to stimulate patient inclusion, as patients have a higher chance to randomise for the intervention group. Furthermore, more determinants can be included in a prediction model for successful dose reduction if the intervention group is larger. Patients will be stratified on comedication use (yes/no), as the incidence of flares could possibly be different with or without comedication use. Comedication includes azathioprine, 6-mercaptopurine, 6-thioguanine, methotrexate. Both patients and physicians are un blinded, as we aim to represent daily practice during this pragmatic study.

